## Background

Anorectal diseases are mostly benign and do not affect life expectancy, so currently both patients and clinicians are extremely interested in performing day care surgery. Anorectal surgery itself causes certain discomfort, especially pain, long recovery period, and a decreasing quality of life for several months.

The pain appears as a result of endogenous and exogenous factors affecting on the peripheral nerves endings, and also the pathological central nervous system excitation. Any surgical intervention activates nociceptors with various stimuli including mechanical factors as a result of a prick or cut of the tissue, chemical factors as a result of exposure to inflammatory mediators, and thermal factors as a result of heating or cooling the tissue [1]. Thus, any surgery is always accompanied by a pain syndrome with various pain severities.

In anorectal surgery, almost every patient experiences moderate/severe pain in the postoperative period, 12% of patients have severe pain throughout the recovery period, and control of postoperative pain is still problematic in 5% of cases when a severe pain syndrome continues despite standard pain management. It leads to long hospital admission and to an opioid intake increase [2]. The problem of analgesia is still relevant for patients after anorectal surgery, because the diseases affect more than 50% of the population over 50 years [3]. Excisional hemorrhoidectomy is the most effective method of stage III–IV hemorrhoidal disease treatment. However it is associated with intense postoperative pain which decreases significantly the quality of life in the postoperative period and overall patients’ satisfaction with treatment, increases time spent in hospital, and opioid analgesics consumption [2, 4]. The pain after hemorrhoidectomy (HE) and other anorectal surgery depends on anal sphincter and puborectal muscles spasm, the type of intra- and postoperative anesthesia, wound healing, surgical technique, stool type, and patient’s subjective perception [5, 6]. According to pain management international guidelines, the target level of postoperative pain should be 3–4 or less visual analog score (VAS) points [7].

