### The main outcome measures

The trial is conducted to evaluate the primary outcome: the quantity of the opioid administration intake per day during the first week postoperatively that is necessary to hold pain level no more than 3–4 VAS points in every patient. We use tramadol as an opioid analgesic in a single standard dose of 100 mg for patients with persistent severe pain syndrome in our clinic. The study also assesses the following secondary outcomes: (1) the pain severity before and after defecation according to VAS on the 6, 12, and 24 h after the procedure, then 2 times per day up to 7th postoperative day; (2) duration and (3) frequency of other analgesics intake (systemically and topically) during the first week postoperatively; (4) readmission rate and (5) overall quality of life on the 7th and 30th days; (6) time from the procedure to return to work; and (7) the complications rate (i.e. bleeding, retention of urine, infectious complications) in the early postoperative period (30 days after procedure). The pain severity, duration and frequency of other analgesics intake during the first week postoperatively will be assessed using “Postoperative protocol for pain management” (Additional file 2). The overall quality of life will be assessed with a patient-reported questionnaire Short Form 36 (SF-36). A total score in each of the 8 sections will be calculated and transformed into a 0–100 scale with a score of zero equivalents to maximum disability and a score of 100 equivalents to no disability. Other secondary outcomes will be updated during visits or by phone on the 7 and 30 days after the surgery.

All patients are scheduled to return to the ambulatory clinic on the 7 and 30 days after the surgery. During these visits, postoperative data is collected and digital rectal examination is performed. If a patient fails to follow up, the researcher may contact the patient by all means available (phone, email, or mail) to ascertain whether the patient has had any complications and/or adverse events that were treated at another hospital. If the researcher is unsuccessful in contacting the patient, the patient will be considered as lost to follow-up.

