**Table 1 Tab1:**
[figure not shown]
Schedule of enrollment, interventions, and assessments

*Follow-up (1)—the first postoperative day

**Follow-up (2)—the first week after the procedure

***Follow-up (3)—postoperative day 30

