### Statistics

The ITT analysis included all randomized patients treated for at least 1 week, who were evaluated for efficacy at baseline and at least once at subsequent evaluation points during the study. The PP-analysis will exclude from the full analysis all the non-compliant patients, patients who received incomplete treatment, and patients who refused further treatment after randomization.

Quantitative variables are described as means with standard deviations, medians, range, or interquartile range as appropriate. Categorical variables are described in absolute numbers and percentages. The statistical analysis of the quantitative variables, with independent groups, is performed with the parametric Student’s *t* test, providing that its conditions for application are met. Otherwise, the non-parametric Mann-Whitney *U* test is used. Statistical analysis for categorical variables is performed using the Pearson *χ*^2^ test or the Fisher exact test. Specifically, the above methods are used to compare the two groups in terms of baseline characteristics in order to assess whether the randomization has been effective. Ninety-five percent confidence intervals for the ratio will be reported. In all cases, the level of significance will be the usual 5% (*α* = 0.05).

This study has a low risk of selection bias due to the use of a computer random number generator. Central allocation and the use of sequentially numbered drug containers of identical appearance allow to achieve a low risk of deviations. Performance bias may be considered as having an average risk due to blinding only participants of the study, the personnel is not blinding. Blinding of outcome assessment is ensured, so detection bias is unlikely. Attrition bias could probably appear because of the difficulty of collecting data from patients outside the hospital or the refusal of future treatment and visiting the doctor during follow-up.

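### Time to return to work is followed only to the day-30 contact, but the stated t test and Mann-Whitney rule makes no allowance for times not observed by then, which can shrink the mean difference and cost power

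*Protocol article*

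**What the plan says.** The section on the main outcome measures lists "time from the procedure to return to work" as the sixth of seven secondary outcomes. It sets no horizon for this outcome and no rule for a patient who has not gone back. On data collection it says "Other secondary outcomes will be updated during visits or by phone on the 7 and 30 days after the surgery". The notes to Table 1 give the last assessment as "Follow-up (3)—postoperative day 30".

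The Statistics section has one general rule. "The statistical analysis of the quantitative variables, with independent groups, is performed with the parametric" Student's t test, if its conditions are met; "Otherwise, the non-parametric Mann-Whitney" U test is used. No survival method appears, and no test is assigned to return to work by name. The same section defines an intention-to-treat set that needs one week of treatment and at least one evaluation after baseline, and it warns: "Attrition bias could probably appear because of the difficulty of collecting data from patients outside the hospital". The Background speaks of a "long recovery period, and a decreasing quality of life for several months" after anorectal surgery.

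**The concern.** Time to return to work is right-censored by design. For a patient still off work at the day-30 contact, all that is known is that the time exceeds 30 days. A patient seen on day 7, still off work and then lost is in the analysis set with even less information. A t test needs a number for each patient, so the analyst must exclude these patients or assign them a value. Exclusion removes the slowest returners and takes more of them from the slower arm, so it hides part of any true benefit. Assigning a value near 30 also understates the difference in mean time.

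At stake is one secondary outcome: the size of the reported difference, the chance of detecting it, and a choice between handling rules that would otherwise be made late. The primary outcome and the sample size are not affected.

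**Working it through.** The protocol gives no figure for this outcome, so there is none to reproduce. The check asks how much the handling of off-work patients matters under stated assumptions.

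**Inputs from the article.** 72 patients per arm (Sample size); 5% significance level and the two tests (Statistics); last contact on day 30 (main outcome measures and Table 1 notes).

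**Assumptions, not in the article.** Log-normal times rounded up to whole days, log-SD 0.5, ketoprofen median 0.8 times the control median, control medians of 10 to 26 days, two-sided testing, no loss before day 30, and 1,500 simulated trials per scenario. The Monte Carlo standard error of a power near 0.7 is √(0.7 × 0.3 / 1500) ≈ 0.012.

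**Off-work share.** P(T > 30) = 1 − Φ(ln(30/median)/0.5). For medians of 16 and 12.8 days:
- Control: 1 − Φ(1.257) = 0.104.
- Ketoprofen: 1 − Φ(1.704) = 0.044.

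The simulation gave 0.104 and 0.045.

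**True mean difference.** Control median × exp(0.5²/2) × (1 − 0.8). For a control median of 16 days this is 16 × 1.133 × 0.2 = 3.6 days, as simulated.

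**Power.** Excluded means off-work patients are dropped. Tied or capped means all of them take one common value above 30.

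| Control median (days) | Off work at day 30, control/ketoprofen | Mann-Whitney, excluded | t, excluded | Mann-Whitney, tied worst rank | t, capped | Log-rank, censored at day 30 |
|---|---|---|---|---|---|---|
| 10 | 1/0% | 0.71 | 0.70 | 0.74 | 0.72 | 0.68 |
| 12 | 3/1% | 0.67 | 0.65 | 0.71 | 0.71 | 0.67 |
| 16 | 10/5% | 0.58 | 0.57 | 0.73 | 0.73 | 0.68 |
| 20 | 21/10% | 0.49 | 0.49 | 0.74 | 0.74 | 0.70 |
| 26 | 39/23% | 0.33 | 0.34 | 0.72 | 0.72 | 0.69 |

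With every time observed, Mann-Whitney power would be 0.71 to 0.75 throughout.

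**Mean difference in days.**

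| Control median (days) | All times observed | Excluded | Capped |
|---|---|---|---|
| 10 | 2.3 | 2.0 | 2.2 |
| 12 | 2.7 | 2.2 | 2.5 |
| 16 | 3.6 | 2.2 | 3.0 |
| 20 | 4.6 | 2.2 | 3.3 |
| 26 | 6.0 | 1.9 | 3.1 |

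**No true effect.** With about 10% or 39% off work in both arms, every method rejected in about 4% to 6% of runs.

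**Reading.**
- The power loss comes from exclusion. Both stated tests keep their power when off-work patients stay in at a common value.
- The estimate shrinks either way. At 21/10% it falls from 4.6 to 2.2 days under exclusion and to 3.3 under capping.
- Loss before day 30 was not simulated. Such patients cannot share a worst rank, because they may have returned soon after their last contact. The size and direction of that effect depend on who is lost.

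**The case against.** The strongest reply is that Mann-Whitney, which the plan already names, copes with a common day-30 cut-off. Every off-work patient is known to exceed 30 days, so all can share the worst rank. In these scenarios that gives power of 0.71 to 0.74, slightly above the 0.67 to 0.70 of log-rank. This stands. A reader might infer that neither stated test can handle patients still off work. For Mann-Whitney at a common cut-off, that is wrong.

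A reader might also infer that bias and lost power are certain. The article does not support that. It nowhere orders exclusion, and it gives no off-work share. At 1 to 3% off work, exclusion costs about 1 to 5 points of power against full observation and nothing against log-rank. Nor is there support for expecting false positives, since type I error held under equal censoring.

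It is fair to add that the day-30 limit is inferred from the contact schedule, and that handling rules are often left to an analysis plan. The second point carries only part of the way. The article does more than stay silent: it states a rule for all quantitative variables whose first choice compares means, and it expects loss to follow-up. Worst ranks do not solve early loss, and they do not give an estimate in days.

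**Conclusion.** The point holds in conditional form. For an outcome that ends at the day-30 contact, the stated rule is poorly suited to unobserved times. If a material share of patients is off work at day 30, a t-test mean difference is pulled toward zero whether they are excluded or capped. It loses roughly half its size under exclusion at 21/10% off work and about two thirds at 39/23%. Exclusion also lowers Mann-Whitney power to about 0.58, 0.49 and 0.33 at 10/5%, 21/10% and 39/23%, against 0.68 to 0.70 for log-rank. At 1 to 3% the matter is minor.

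These sizes rest on assumed log-normal times, a median ratio of 0.8 and no early loss. The case for change is a clearly defined estimate and proper use of patients lost before day 30, not a gain in power over worst-rank Mann-Whitney. It is worth correcting before unblinding, as an issue for one secondary outcome.

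**What to change.** Add to the Statistics section that time to return to work is analysed, in patients who were working before surgery, by Kaplan-Meier curves and a log-rank test. Patients not yet back are censored at day 30 or at last contact if earlier. Report the between-group difference in restricted mean time to day 30 with a 95% confidence interval. This is preferable to a hazard ratio because hazards may not be proportional. It will be smaller than a difference in unrestricted means, but it is labelled for what it measures.

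The cost is a short addition to the text and one data item. Pre-surgery working status is not among the listed baseline characteristics, and patients up to 75 years old are eligible, so it must be recorded at baseline or asked at a follow-up contact. Non-working patients leave this one secondary analysis. The log-rank test still assumes that loss is unrelated to return time within each arm, so early losses should be reported by arm.

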**Discussion:**

Multimodality pain management has been shown to improve pain control and decrease opioid intake in patients after hemorrhoidectomy in several studies. Gabapentin can be considered as an alternative approach to pain control as NSAIDs have limitative adverse effects. Systemic admission of ketorolac with local anesthetics also showed significant efficacy in patients undergoing anorectal surgery. We hope to prove the efficacy of multimodal analgesia including preemptive one for patients undergoing excisional hemorrhoidectomy that will help to hold postoperative pain levels no more than 3–4 points on VAS with minimal consumption of opioid analgesics.

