### Eligibility criteria

Every patient included in the study must meet the following criteria:
Symptomatic hemorrhoids grade III–IVPlanned surgery: Milligan-Morgan hemorrhoidectomy

Patients who had contraindication or technical inability to perform subarachnoid anesthesia or other somatic diseases (history of peptic ulcer diseases and gastrointestinal bleeding and other acute or decompensated organ pathology) or refused to participate and pregnant women are not included. The written voluntary informed consent to participate (Additional file 3) is obtained from all eligible patients before randomization.

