### Interventions

#### Preoperative preparation

Two hours before the procedure, every patient receives a medication. The research group receives ketoprofen 100 mg per os; the control group receives a placebo.

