#### Postoperative period

After the procedure, all patients receive the standard analgesics scheme. It includes ketoprofen (the average dose, 100 mg per day; the maximum dose, 200 mg per day), paracetamol (at the maximum dose of 1000 mg per day), and local anesthetics with lidocaine before defecation. Patients are usually discharged on the 4–5th day after surgery when their pain level is below 5 points according to VAS. After discharge, a standard analgesics scheme mentioned above is recommended to all patients. If the pain level reaches 5–6 points according to VAS on the 5th day after the procedure, patients continue inpatient treatment and may receive an opioid analgesic.

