### Data monitoring

There is no data monitoring committee designated for this trial. Any adverse and serious adverse events will be immediately reported to the principal investigator and the primary sponsor. Participants’ names and collected data are subject to medical confidentiality. In cases of withdrawal, collection of data will cease but not be erased. A logistics database with a patient’s complete ID will be used and kept within a separate password-protected system from the results database with all study information. At the end of the trial, the original peri-operative package and database will be archived by the principal investigator, who is responsible for providing data to the trial investigators.

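### The safety outcome starts after surgery and names three complications, so events from tablet intake to the end of the operation, and unlisted drug-related events, fall outside the stated comparison by arm

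*Protocol article*

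**What the plan says.** Under Preoperative preparation, "Two hours before the procedure, every patient receives a medication", and the randomised contrast is one dose: "The research group receives ketoprofen 100 mg per os; the control group receives a placebo". Under Postoperative period, "After the procedure, all patients receive the standard analgesics scheme", and that scheme contains ketoprofen in both arms.

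The outcome that counts harms by type is number 7 in The main outcome measures: "7) the complications rate (i.e. bleeding, retention of urine, infectious complications) in the early postoperative period (30 days after procedure". The list is introduced by *i.e.*, so it reads as complete. No site is given for bleeding.

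The Eligibility criteria section excludes, among others, patients with a "history of peptic ulcer diseases and gastrointestinal bleeding". The Discussion paragraph of the Abstract suggests gabapentin as an alternative "as NSAIDs have limitative adverse effects".

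The Data monitoring section states: "Any adverse and serious adverse events will be immediately reported to the principal investigator and the primary sponsor". It sets no start time and no limit by type, but it names no outcome and no comparison by arm.

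The Statistics section limits the ITT analysis to randomised patients with at least a week of treatment, an efficacy assessment at baseline and at least one later. The per-protocol analysis removes those who were non-compliant, had incomplete treatment or refused further treatment.

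**The concern.** The tablet is the only thing that differs by randomisation. A safety comparison of the arms would normally start when the tablet is taken and would include the kinds of harm the drug might cause. Outcome 7 starts later and names three complications that are also common concerns of the operation itself.

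At stake is what the trial can report about the safety of the preoperative dose. If the article is followed as written, a reaction to the tablet in the two hours before surgery, or heavier bleeding during the operation, would reach the investigator but would not enter the stated between-arm result. The same holds for a later drug-related event that is not on the list. A patient who stopped because of such an event could also be missing from both stated analysis sets.

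**Working it through.** The article gives no figure on this point, so there is none to reproduce. The check sets the sections side by side.

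**1. Timing.** Tablet intake is at −2 h (Preoperative preparation). Outcome 7 runs from after the procedure to day 30. The uncovered interval is 2 h + T, where T is the operating time, which the article does not give. If a reaction led to surgery being cancelled, there would be no procedure and the window would never open.

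**2. Content.** Each type of event against the two rules:

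| Event | Reported under Data monitoring | Counted in outcome 7 |
|---|---|---|
| Reaction to the tablet before surgery | Yes | No: before the window and not listed |
| Bleeding during the operation | Yes, if classed as an adverse event | No: before the window |
| Ulcer, renal or hypersensitivity event after surgery | Yes | No: not listed |
| Gastrointestinal bleeding after surgery | Yes | Unclear: no site stated |
| Wound bleeding after surgery | Yes | Yes |

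Readmission is a separate outcome (number 4), but it can only arise after discharge and does not close the early gap.

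**3. Comparison by arm.** Outcome 7 is a categorical outcome and would be compared by the Pearson or Fisher test named in Statistics. The adverse events reported under Data monitoring are not among the seven secondary outcomes, and the article states no comparison of them.

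**4. Who is counted.** The Statistics section states two sets, ITT and per-protocol. A patient who takes the tablet, has an adverse event and stops within the first week fails the one-week condition of the ITT set. The same patient also fails the per-protocol set, as incomplete treatment or refusal.

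**5. What 72 per arm can show.** The event rates here are assumptions, since the documents give none. The chance of seeing at least one event among 72 patients is 1 − (1 − p)^72:

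- p = 0.5%: 30%
- p = 1%: 52%
- p = 2%: 77%
- p = 5%: 98%

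With no events among 72, the one-sided 95% upper bound is 1 − 0.05^(1/72) = 4.1%. A table by arm would therefore describe rare harms without settling them.

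**The case against.** The strongest reply is that nothing is lost. Any adverse event is reported, operation notes go into the eCRF, and when a patient misses follow-up the researcher asks about adverse events as well as complications. Collection windows and tables by arm are often left to a full protocol or analysis plan, and the body of Table 1 is not visible. This stands as far as recording goes: it would be wrong to say that the trial misses these events. It does not answer the point about the outcome, because the article itself fixes the start, the list and the analysis sets.

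The Data collection section also says that data from before a patient's exit will be analysed. That pulls against the one-week condition, but the article does not say which statement governs.

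Three stronger readings are tempting and are not supported:

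- A reader might infer that the uncovered interval is the whole time in which only one arm has had ketoprofen. The first postoperative dose is not timed, so unshared exposure may continue into the window, and a tablet effect that appears after surgery is counted if it is on the list.
- A reader might infer that gastrointestinal harm is left out altogether, or that ulcer patients were excluded because of the drug. Bleeding has no stated site and may include gastrointestinal bleeding, and the exclusion is listed without a reason.
- A reader might use the tablet's share of total ketoprofen as the size of the problem. A dose share does not measure missed events, and dilution by shared postoperative ketoprofen would affect any outcome that runs to day 30.

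It is also fair that the stated objective is efficacy and that no claim of safety equal to placebo is planned.

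**Conclusion.** The point holds as a mismatch between the randomised exposure and the stated safety outcome. The comparison by arm leaves out the interval from tablet intake to the end of the operation (2 h plus an unstated operating time) and any drug-related event not on the list of three. It leaves the meaning of bleeding open. The one-week condition can also remove a patient who stopped because of an early event.

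This rests on reading *i.e.* as a closed list, on counting the 30 days from the procedure as the text says, and on applying the stated ITT and per-protocol sets to the safety outcome, since the article names no other set.

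The number of events affected cannot be estimated from the document. The primary outcome does not depend on this point. It is a cheap improvement.

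**What to change.** Redefine the safety window to run from tablet intake to day 30. State the site of bleeding in outcome 7: intraoperative, wound or gastrointestinal. Add one table of the adverse events already reported under Data monitoring, by arm, for all patients who took the tablet, whether or not they completed a week of treatment or went on to surgery. Say in the Statistics section that this set, and not the ITT set, is used for safety, and reconcile it with the statement that data from before a patient's exit will be analysed.

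The cost is a change of outcome wording, a few eCRF fields and one extra table. The reports and the operation notes are already collected. The table should be presented as descriptive for rare harms.
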